#### Questionnaire and study module translation

The forward and back translation processes will be utilised, to translate the study’s English-language questions. All queries are initially translated from English into Arabic. Subsequently, a professional linguist will translate the original questionnaire, from English to Arabic, in the forward direction (native speaker of Arabic and expert in English). A separate impartial, knowledgeable, and skilled translator will then perform the reverse translation from Arabic to English (native speaker of Arabic and expert in English). To remove the possibility of any discrepancy between the items in the original and translated versions, another English language translator is brought into the picture, to compare the back-translated English version with the original questionnaire. Ultimately, the accuracy, of the final version of the module and questionnaire, is verified by the researcher, through a comparison between the translated version, and the original text.

### Statistical analysis

Data analysis will be conducted using the statistical package for social sciences (SPSS) software version 26 for Microsoft Windows (Chicago, IL, USA). An inspection for omitted values and outliers will be conducted prior to data analysis. Descriptive statistics will be applied for the presentation of the data to determine means, median, standard deviations (continuous variables), frequencies, and percentages, to represent categorical data (categorical variables). The normality of variables will be described among continuous data by way of the Kolmogorov- Smirnov test, as well as the Skewness & Kurtosis test. In the Kolmogorov- Smirnov test, a P-value > 0.05 is an indication of normal data distribution. Data not normally distributed, will be transformed into a categorical variable. In the Skewness & Kurtosis test, -1.96 to +1.96 is deemed normal data.

One Way ANOVA will be used, to determine whether any significant within-group variances occurred over time, for the selected variables, if the data is normally distributed, while Friedman’s test will be used, to determine whether any significant within-group variances occurred over time, for the selected variables, if the data is not normally distributed.

The generalized estimating equation (GEE) will be used, to test the effect of the nutrition intervention program, on the selected variables (outcomes), between & within the group, at baseline, six weeks, and two months following intervention, which is adjusted for clustering. Missing data will not be replaced. Outcomes will be assessed at each time point, along with derived average overall three-time points, thus ensuring the delivery of both the cumulative and overall effects.

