### Study outcomes

#### Primary outcome

The knowledge, attitude, and practice of nutrition and physical activity questionnaire (KAP-Q) will be used, to measure the primary outcome of interest for this study, in accordance with the approach employed by Sharif Ishak et al. [31] and Harake et al. [32]. The questionnaire consists of 73 items: knowledge (30), attitude (22), and practice (21). The knowledge section serves to determine the participants’ level of comprehension, regarding nutrition and physical activity. The response options to the multiple-choice questions in the questionnaire are ‘True’, ‘False’ and ‘I do not know’. Correct responses will be designated ‘1’, while incorrect and ‘I do not know’ responses will be designated ‘0’. The maximum score is 30, and the minimum 0. A score above the mean is an indication of good knowledge. The five Likert scale responses for assessing attitude are ‘strongly agree’, ‘agree’ ‘neutral’, ‘disagree’, and ‘strongly disagree’. Eleven negatively termed questions will be inversely recoded during data analysis. The maximum score is 110, and the minimum 22. A higher score is an indication of a greater positive attitude. The practice section includes 21 questions, which come with five Likert scale responses: ‘very frequently’, ‘often’, ‘sometimes’, ‘rarely’, and ‘never’. Nine negatively termed questions will be inversely recoded during data analysis. The maximum score is 105, and the minimum 21. A higher score is an indication of a more positive practice.

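### A normality pre-test on the trial's own data decides whether the primary KAP outcome is analysed as a score or as a category, under two unreconciled criteria and without usable cut-points

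*Protocol article*

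**What the plan says.** All statements are in the protocol article.

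- **Rule (Statistical analysis).** "Data not normally distributed, will be transformed into a categorical variable". No outcome is exempted, and the number of categories and the cut-points are not given.
- **First criterion (Statistical analysis).** "In the Kolmogorov- Smirnov test, a P-value > 0.05 is an indication of normal data distribution".
- **Second criterion (Statistical analysis).** "In the Skewness & Kurtosis test, -1.96 to +1.96 is deemed normal data". The text does not say which criterion decides, or which group or time point is tested.
- **Another treatment of non-normal data (next paragraph).** For such data, "Friedman’s test will be used, to determine whether any significant within-group variances occurred over time".
- **Between-group analysis (Statistical analysis).** A GEE adjusted for clustering is named, with no normality condition and no statement of which form of the outcome enters it.
- **Primary outcome (Study outcomes).** There are three KAP section scores: knowledge, attitude (22 to 110) and practice (21 to 105). For knowledge, "The maximum score is 30, and the minimum 0". The only KAP category is for knowledge: "A score above the mean is an indication of good knowledge".
- **Secondary outcomes.** PAQ-C, ASAQ, EAT-26 and BMI have fixed cut-offs.

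**The concern.** The form of the primary endpoint should be fixed before the data are seen. Under this rule it is the output of a preliminary test. The same trial could report a mean difference for attitude and a proportion for knowledge, or different forms at different visits. Because the two criteria can point in opposite directions, either form could be defended afterwards. Once a score is to be categorised, someone must also choose cut-points for attitude and practice, and the document supplies none.

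The conversion also discards information and buys nothing in return, since GEE estimation does not require a normally distributed outcome.

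**Working it through.** **Step 1. Can the two criteria disagree?** The document gives no KAP means, SDs or shapes, so the values below are assumptions. Scores were simulated, rounded to integers and tested by Kolmogorov-Smirnov with estimated mean and SD (Lilliefors form) at n = 250.

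| Simulated score | Kolmogorov-Smirnov rejects | Raw skewness and kurtosis within ±1.96 |
|---|---|---|
| Knowledge, normal, SD 3 | 100% | 100% |
| Knowledge, normal, SD 4 | 96% | 100% |
| Knowledge, normal, SD 5 | 76 to 78% | 100% |
| Attitude, normal, SD 8 to 12 | about 15 to 35% | 100% (run at SD 10) |
| Attitude, skewness about -0.5, SD 10 | 79% | 98% |

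At n = 125 (each arm tested separately), knowledge is rejected in 36 to 89% of samples. If the uncorrected Kolmogorov-Smirnov test is used instead, knowledge at n = 250 is rejected in only about 5 to 59%. The article does not name the form.

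The second criterion is ambiguous too. A skewness of -0.5 lies inside ±1.96 as a raw statistic. Divided by its approximate standard error, √(6/250) = 0.155, it gives -0.5/0.155 = -3.2, which lies outside. So the path depends on which test, which form and which sample are used, and none of these is fixed.

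**Step 2. Are there cut-points to use?** Knowledge has a mean of unstated origin (which group, which visit). Attitude and practice have none.

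**Step 3. Cost of a two-category split, independent pupils.** For a normal score cut at standardised point c, retained information = φ(c)²/[P(1-P)]. At the centre this is 2/π = 0.637, and 1 SD off centre it is 0.44. Equal thirds keep 0.79 and equal quarters 0.86.

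**Step 4. Cost after clustering.** The Sample size section gives ICC 0.05 and design effect 2.2, which reproduces with 1 + 0.05 × (25 - 1) = 2.2, so m = 25. Four schools and 250 pupils give 250/4 = 62.5 per school.

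A median split lowers the ICC to (2/π) × asin(0.05) = 0.0318. Retained information = 0.637 × (design effect of score)/(design effect of split).

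- m = 25: score 2.20; split 1 + 24 × 0.0318 = 1.76; 0.637 × 2.20/1.76 = 0.79.
- m = 62.5: score 1 + 61.5 × 0.05 = 4.08; split 1 + 61.5 × 0.0318 = 2.96; 0.637 × 4.08/2.96 = 0.88.

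**Step 5. Power.** For a comparison with 80% power on the score, power after the split = Φ[(1.96 + 0.84) × √(retained) - 1.96].

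- Retained 0.79: Φ(0.53) = 70%.
- Retained 0.88: Φ(0.66) = 75%.
- Independent pupils, 0.637: Φ(0.27) = 61%.

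The 80% is a reference point only. The article's sample size rests on overweight proportions and gives no power for KAP.

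**The case against.** Several stronger readings are tempting, and the document does not support them.

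- **That categorisation would be the usual path.** This holds for knowledge only if Kolmogorov-Smirnov in the Lilliefors form governs. The second criterion, read as raw statistics, would leave almost all of the simulated scores as scores. Attitude would mostly pass Kolmogorov-Smirnov as well unless it is skewed.
- **That 36% of the information, or about 90 of 250 pupils, would be lost.** That figure is for independent pupils and two categories. Clustering reduces the loss to about 12 to 21%, and the article does not say that two categories would be used.
- **That the knowledge cut moves with the data, so that visits cannot be compared.** This follows only if the mean is recomputed at each visit. The text does not say so, and does not tie the knowledge label to the categorisation rule.
- **That the Friedman sentence flatly contradicts the rule.** It concerns within-group change only, and a rank test can be run on ordered categories. The article does not say that it uses the original values. The two treatments need reconciling, but they are not strictly incompatible.

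It can also be said that cut-points may stand in an analysis plan that is not shown, and that several secondary outcomes already have fixed cut-offs. Both points are fair. Neither rescues the rule, which is stated outright, covers the primary outcome, and makes its form depend on the data wherever the cuts are kept.

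**Conclusion.** The point holds and should be changed. As written, a pre-test on trial data selects the form of the primary KAP outcome. The two criteria can disagree with no tie-break, and the cut-points are missing for attitude and practice and unclear for knowledge. This part rests on the text alone.

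The size is conditional. If a two-category split near the median were used, about 79 to 88% of the information would remain, and 80% power would become about 70 to 75%. This assumes near-normal scores, the planning ICC of 0.05 applied to KAP, 25 to 62.5 pupils per school and normal-theory power, which is optimistic with four schools. An off-centre cut would cost more, and three or four categories less. How often the rule would be triggered cannot be known from the document. The rejection rates only show that the two criteria can conflict.

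**What to change.** Delete the categorisation sentence. State that KAP knowledge, attitude and practice, and the PAQ-C and HBQ scores, are analysed as scores in the GEE with robust variance, whatever the normality checks show. With only four schools the robust variance has a small-sample problem of its own. That is a separate matter, and categorising does not cure it.

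For clearly skewed outcomes, name a suitable link or scale in advance. A plain log will not do where zeros can occur, as in EAT-26.

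Keep categorical versions as pre-specified supplementary summaries at fixed cut-points, for example the stated EAT-26 threshold of 20, and not at a sample mean. If normality checks are kept for the within-group tests, say which criterion governs and what data Friedman's test is run on.

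The cost is wording only: no extra pupils, visits or measurements.

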### Study setting

Conducted in Arabic schools located in the Klang Valley, this study involves students in grades seven and eight. There are a total of 25 Arabic schools in the Klang Valley, an urban region in Malaysia, with its centre in Kuala Lumpur. Excel software will be used for the random selection and allocation of 4 out of these 25 Arabic schools. The first two schools are assigned intervention groups, while the next two are assigned control groups. Subsequently, 4 classes will be randomly selected from each school. Two of these classes will consist of 13-year-old seventh-grade students, while the next two will consist of mostly 14-year-old eighth-grade students.

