### Sample size

The cluster randomized control trial formula was applied to calculate the sample size, taking into consideration a power of 80%, and a 95% confidence level [28]. According to the proportion of overweightness among adolescents, calculated in a previous study conducted by James et al. [29]:

$$n=DE\times (Z_{1‐\alpha /2}+Z_{1‐\beta })\frac{2P1(1-P1)+P2(1-P2)}{(P1-P2)2}$$

DE = 1+ *p* (m-1)

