### Sampling method

Simple random sampling will be used for the selection of participants. Two schools will be assigned the intervention group, and two schools the control group, followed by the selection of classes. With this form of probability sampling, researchers use a sampling frame, which includes a list of all students from the selected schools. For this study, a table of random numbers, will be used for the selection of participants, up to the point the sample size is attained. The random selection of participants is achieved by way of Excel software.

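### With two randomised schools per arm, the GEE test rests on four clusters: the usual uncorrected robust Wald test by school has about 30% type I error at a nominal 5%

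*Protocol article*

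**What the plan says.** Under Study setting, the protocol article fixes the number of randomised units: "Excel software will be used for the random selection and allocation of 4 out of these 25 Arabic schools". It continues: "The first two schools are assigned intervention groups, while the next two are assigned control groups". Sampling method repeats this: "Two schools will be assigned the intervention group, and two schools the control group, followed by the selection of classes". The Randomization paragraph also describes drawing four school envelopes. Classes are sampled afterwards, within schools already allocated: "Subsequently, 4 classes will be randomly selected from each school".

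Under Statistical analysis, the test of the intervention is stated as "The generalized estimating equation (GEE) will be used, to test the effect of the nutrition intervention program, on the selected variables (outcomes"), applied "at baseline, six weeks, and two months following intervention, which is adjusted for clustering". The text does not name the cluster unit, the variance estimator or the reference distribution. Sample size works at 80% power and a 95% confidence level, with ICC 0.05 and 250 pupils in total, 125 per arm.

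**The concern.** The comparison between arms is a comparison of two schools with two schools. Sampling more pupils or classes in those schools makes each school mean more precise but adds no independent unit at the level of randomisation. The robust variance in GEE is justified when clusters are many. With two per arm it is biased low, and referring the statistic to a normal distribution adds to the error.

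At stake are the between-group p-values and confidence intervals for every outcome tested this way, including the primary knowledge, attitude and practice (KAP) scores. An ordinary difference between schools could be reported as an effect of the programme.

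**Working it through.** **Inputs.** From the protocol article: 4 schools, 2 per arm, and 4 classes per school (Study setting); 250 pupils, hence 250/4 = 62.5 per school, and ICC 0.05 (Sample size). The ICC belongs to a calculation on the proportion overweight, so using it for the KAP scores is an assumption. The article states no type I error for the GEE beyond the 95% confidence level, so there is no figure of its own to reproduce.

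**1. GEE clustered on school, uncorrected robust Wald test.** Take two equal schools per arm and let S be the sum, over both arms, of squared deviations of school means from their arm mean.
- Sandwich variance of the arm difference: S/2² = S/4.
- Unbiased variance: the pooled between-school variance is S/2 on 2 df, and multiplying by (1/2 + 1/2) gives S/2.
- The sandwich variance is therefore half the unbiased one, so z = √2 × t on 2 df.
- Type I error = P(|t₂| > 1.96/√2) = P(|t₂| > 1.386) = 1 − 1.386/√(2 + 1.386²) = 0.300.

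The ICC cancels. Simulated school means (40,000 runs per value) gave 0.297 to 0.304 for ICC 0 to 0.10. Fitted three-wave GEE models at ICC 0.05 (500 runs each, Monte Carlo SE about 0.02) gave 0.31 to 0.33 with equal schools and 0.29 to 0.32 with unequal schools.

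**2. Small-sample corrections, same clustering.**

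| Variance | Reference | Type I error |
|---|---|---|
| Uncorrected | normal | 30% |
| Scaled by 4/3 | normal | 25% |
| Unbiased (×2) | normal | 19% |
| Leverage-squared correction (×4) | normal | 11% |
| Uncorrected | t, 2 df | 9% |
| Unbiased (×2) | t, 2 df | 5% |

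**3. Clustering on class or pupil.** For a post-only comparison at school ICC 0.05, the error is about 31% by class and 32 to 34% by pupil. At ICC 0.01 it is 16% and 11%.

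The plan includes a baseline wave, and a school difference that is constant over time cancels from a change score. Assume total variance 1, school variance 0.05, within-pupil correlation 0.6 and 62 pupils per school (124 per arm), and let f be the fraction of the school variance that varies over time.
- Pupil part of the change variance: 2 × 0.4 × 0.95 = 0.76.
- True variance of the arm difference: 2f(0.05) + 2(0.76)/124.
- Variance a pupil-level test would use: about 2(0.76 + 0.05f)/124.

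| f | True variance | Variance used | Type I error |
|---|---|---|---|
| 0 | 0.0123 | 0.0123 | 5% |
| 0.2 | 0.0323 | 0.0124 | 22% |
| 1 | 0.1123 | 0.0131 | 50% |

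A simulation of 4,000 runs per row gave 5%, 22% and 50%.

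**4. Power with a valid test.** For t on 2 df the critical value is 4.30. At ICC 0.05, the SE of the difference in school means is √(0.05 + 0.95/62.5) = 0.255 SD. Power from the non-central t is 21% for 0.5 SD and 41% for 0.8 SD, and 80% needs about 1.4 SD. These figures take no credit for baseline adjustment, which could reduce the SE.

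**5. A mixed model as an alternative.** The REML school variance is zero when the between-school mean square falls below the within-school one. Their expected ratio is (0.95 + 62.5 × 0.05)/0.95 = 4.29, so the chance is P(F₂,₂₄₆ < 1/4.29) = 0.21. In about one trial in five the model would show no school component.

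**The case against.** The strongest reply is that the article never commits to the test that gives 30%. That figure needs three choices: school as the cluster, an uncorrected sandwich, and a normal reference. The text says only that the GEE is adjusted for clustering, and an analysis plan that is not shown could settle all three. This stands as a limit on the number. A reader might infer that the trial will certainly run at 30%, and the document does not support that. The reply does not remove the point, because the article itself fixes both the four randomised schools and GEE as the effect test. A fully corrected test restores 5% only at the power shown above.

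A reader might also infer that clustering on class or pupil gives a similar error. That holds only for a post-only comparison at ICC 0.05. For change from baseline the error can be near nominal or well above 30%, depending on a stability over time that the article does not report.

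A third inference would be that "Missing data will not be replaced" is part of the same fault. It is a separate matter. Available-case GEE tolerates missingness that depends on covariates in the model, and nothing in the article allows the effect to be sized.

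**Conclusion.** The point holds in conditional form. Four randomised schools cannot support a GEE test that relies on large-sample theory. Clustered on school with the usual uncorrected robust Wald test, the type I error is about 30% at any ICC, taking roughly equal schools and normal school means. Partial corrections give about 9 to 25%, and an unbiased variance with t on 2 df gives 5%. Clustering below the school leaves the error uncontrolled: about 5% to 50% for change from baseline with a school variance of 0.05 and a within-pupil correlation of 0.6, both assumed for the KAP scores. The root cause is the number of schools, so no choice of variance estimator gives both a valid test and useful power for moderate effects.

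**What to change.** In Statistical analysis, base between-group claims on an analysis at the level of randomisation. Compute each school's mean outcome adjusted for the pupil's own baseline value, compare two schools with two using t on 2 df, and report that confidence interval. State that no claim rests on an uncorrected GEE Wald test. A linear mixed model with a random school effect and small-sample df may be shown as support only, given how often its school variance would be estimated as zero.

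The cost is more than wording. Intervals widen greatly, because the critical value rises from 1.96 to 4.30, and power for moderate effects is low. The article should say so and describe the trial as giving limited evidence of effectiveness.

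If schools are not yet drawn, spreading the same 250 pupils over more of the 25 schools raises the df, at a logistic cost. Even the uncorrected robust test would then err less: about 14% with 8 schools and 10% with 12. A small-sample method would still be needed.

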**Methods and anticipated results:**

A cluster randomized controlled study will be conducted, involving 250 Middle Eastern adolescents, in Arabic schools in Malaysia. The participants will be randomly assigned to the intervention and control groups. While the intervention group participates in six weeks of fortnightly six sessions (45 minutes per session), the control group will carry on with their regular curriculums, and normal physical activity routines. The variables which will be evaluated include anthropometric measurements, knowledge, attitude, daily routines, physical activity, sedentary behaviour, food assessment, eating attitudes test-26, and a structured questionnaire based on the HBM. Data will be collected from the intervention and control groups at baseline, post-intervention, and two months following the intervention. Data analysis will be performed by way of the SPSS Statistics software version 26. The generalized estimating equation (GEE) will be used, to test the effect of the intervention program, with regards to the selected variables (outcomes), between and within-group at baseline, as well as six weeks and two months following intervention, after adjusting for clustering. Outcomes will be assessed at each time point, along with a derived average over all three-time points; thus, ensuring that both the cumulative and overall effects are determined.

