**where**:

Z_1-α/2 =_ Standard score for (1–0.025) = 1.96Z_1-β =_ Standard score (1–0.20) = 0.84 (80% power)P1 = The proportion of those overweight from control group (p1) = 27.6%P2 = The proportion of those overweight from Intervention group (p2) = 23.1%Intra-cluster correlation (*P*) = 0.05Number of individuals in each cluster (m)DE = Design Effect = 2.2

$$n=2.2\times (1.96+0.84)\;\frac{20.276(1-0.276)+0.231(1-0.23)}{(0.276-0.23)2}$$

Sample size = 220

Adding 15% to the number of subjects as attrition rate = 250

Therefore, the total sample size is 250 participants (125 participants for each group).

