### Data collection

#### Cluster randomized trial flow

*Recruitment of participants*. The teachers and principals will be updated on the study objectives, and the student eligibility criteria, for the cluster randomised controlled trial (RCT). The selection of participants will be conducted at the selected schools. Only those who are available, during the accumulation of data, will be further briefed and assessed on their eligibility, according to the inclusion and exclusion criteria, stated in a screening form. The school administration will forward an invitation, to the parents of eligible participants, to obtain written consent, before the commencement of the study. On receipt of the written consent from students and their parents, the collection of baseline data will begin. The participant information sheet, in English and Arabic, will be made available to eligible students and their parents. The participants will be provided with an explanation, on the objectives and protocols of the study. All participants involved in this study are volunteers, and guaranteed the unrestricted right, to pull out of this study, at any time. Participants will be assured, that all information related to their identities, will be kept confidential. The random selection and allocation of participants, to the intervention or control groups, will be realized through the Excel software. Subsequently, the intervention group will be subjected to the educational intervention. For the post-intervention and follow‐up assessments, the participants will be required to fill in the same questionnaire, albeit, excluding the section referring to personal information.

*Study principles*. This investigation is based on the study protocol item, recommendations for interventional trials (SPIRIT), 2013, statement [23], while complying with the consolidated standards of reporting trials (CONSORTs), statement [30]. The flowchart for the CONSORTs is displayed in Fig 2. CONSORT was developed by a group of researchers not only to identify problems associated with RCTs, but also to present the results of the research in a clear and concise manner, facilitating the reading and assessment of RCTs [30]. The CONSORT 2010 guideline were chosen because it is intended to improve the reporting of parallel- group randomized controlled trials. It enables better understanding of a trial design, conduct, analysis, interpretation and assessment of the validity of its results.

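### GEE on the observed records with no replacement of missing data is not guaranteed unbiased if loss depends on earlier scores differently in the two arms, and 15% attrition is expected

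*Protocol article*

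**What the plan says.** All references are to the protocol article.

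- **Statistical analysis, method:** "The generalized estimating equation (GEE) will be used, to test the effect of the nutrition intervention program". It covers baseline, six weeks and two months, is adjusted for clustering, and reports each time point and an average over all three.
- **Statistical analysis, missing values:** "Missing data will not be replaced". The section mentions no weighting and no assumption about why data are missing.
- **Statistical analysis, non-normal data:** variables that fail the normality check are to be made categorical.
- **Sample size:** "Adding 15% to the number of subjects as attrition rate = 250". The intra-cluster correlation is 0.05.
- **Abstract:** "the control group will carry on with their regular curriculums, and normal physical activity routines", and "Data will be collected from the intervention and control groups at baseline, post-intervention, and two months following the intervention".
- **Cluster randomized trial flow:** "Subsequently, the intervention group will be subjected to the educational intervention". Pupils in either arm may withdraw at any time.
- **Study setting:** four schools, two per arm.

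**The concern.** A GEE fitted to whatever records exist, without weights, is guaranteed consistent only when loss is unrelated to the outcomes once the model covariates are taken into account. Here one arm is asked to attend six sessions and the other is asked for nothing beyond the assessments. A pupil who gains little from the sessions and disengages may also miss the two-month questionnaire. Nothing comparable would drive loss among controls.

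The pupils retained in the intervention arm would then be a favourable selection, and the two-month effect would be overstated. The baseline and post-intervention scores that could correct for this are already collected. Whether the stated analysis uses them depends on a feature, the working correlation, that the stated rule does not secure.

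**Working it through.** **1. The plan's attrition figure.** 220 × 1.15 = 253, close to the stated 250. If 15% of 250 are lost, 250 × 0.15 = 37.5, so about 38 pupils are missing and about 212 remain. (How 220 was reached does not matter for this point.)

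**2. Assumptions for the illustration.** The documents give no dropout mechanism and no within-pupil correlation. Assumed: correlation ρ = 0.6 between assessments; true effect 0.30 SD at both post-baseline assessments; a fraction f = 0.15 lost per arm at two months, at random in controls. In the intervention arm, loss depends on the post-intervention score, with logistic slopes of 0.5, 1.0 or 1.5 per SD. Lost pupils then score d = 0.5 to 1.2 SD lower at post-intervention.

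**3. Check by hand, independence working correlation.** The retained pupils' mean post-intervention score exceeds that of all intervention pupils by f × d. A fraction ρ of this carries to two months, so bias = ρ × f × d.

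- d = 0.5: 0.6 × 0.15 × 0.5 = 0.045, estimate 0.345.
- d = 1.2: 0.6 × 0.15 × 1.2 = 0.108, estimate 0.408.

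**4. Simulation of the same scenario, two-month effect (truth 0.30 SD).**

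| Analysis | Slope 0.5 | Slope 1.0 | Slope 1.5 |
|---|---|---|---|
| GEE, independence | 0.345 | 0.381 | 0.406 |
| GEE, school-level exchangeable (ICC 0.05) | 0.341 | 0.373 | 0.399 |
| GEE, pupil-level exchangeable, normal outcome | 0.304 | 0.300 | 0.302 |
| Analysis valid under missing at random | 0.302 | 0.301 | 0.301 |

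The school-level and pupil-level rows carry a simulation error of about 0.01. In the first row the inflation is 0.045/0.30 = 15% to 0.106/0.30 = 35%.

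**5. Why the school-level GEE behaves like independence.** With 125/2, or about 62, pupils per school and three records each, a record has 185 partners in its school: 2 from the same pupil and 183 from others. The average correlation is (2 × 0.6 + 183 × 0.05)/185 = 10.35/185 = 0.056. A single exchangeable parameter at school level is therefore near the ICC and hardly uses the pupil's own history.

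**6. Average over three time points.** The true value is (0 + 0.30 + 0.30)/3 = 0.20 SD. Only the last term is biased, so the shift is a third: 0.045/3 = 0.015 to 0.106/3 = 0.035 SD.

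**7. Other mechanisms** (separate simulation, true effect 0.3 SD, correlation 0.5 or 0.7, bias in the final-visit difference):

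- Loss completely at random, or differing by arm alone (25% against 5%): about 0.
- Same dependence on baseline in both arms: about 0.
- 15% loss per arm, related to baseline in the intervention arm only: 0.06 to 0.10 SD with independence, about 0 with pupil-level exchangeable.
- 15% loss per arm, related to the unseen two-month outcome in the intervention arm only: 0.12 to 0.13 SD with independence, 0.07 to 0.10 SD with pupil-level exchangeable.

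**The case against.** The strongest reply is that the stated method need not be biased. The article does not commit to an independence working correlation. A pupil-level exchangeable GEE also replaces nothing, yet returns about 0.30 SD in the same scenario. Choosing the working correlation is detail that an article commonly leaves to the full protocol or analysis plan. This stands in part. The missing working correlation is not itself the finding, and a reader who infers that the GEE is valid only under completely random loss goes too far. What remains is that the stated rule does not secure the favourable case. The randomised clusters are schools, and clustering on them in the usual way keeps nearly all the bias. Outcomes made categorical also fall outside the normal-outcome exception.

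A reader might also infer that not replacing data means discarding the earlier scores of pupils later lost. The text does not say so: those records can stay in the GEE and, under a pupil-level correlation, do inform the two-month estimate. Likewise, a mixed model on observed records replaces nothing, so the missing-data sentence is not wrong in itself; the weakness lies in combining it with an unweighted GEE.

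Finally, differential outcome-related loss is conjecture. The 15% is one overall allowance, and the right to withdraw applies to both arms. This stands: session attendance in one arm is a reason to guard against such loss, not evidence of it.

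**Conclusion.** The concern holds in a limited form. The protocol fixes an analysis that is not guaranteed unbiased under outcome-related loss, while planning for about 38 of 250 pupils to be lost and collecting the scores that would protect against it.

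Under the stated assumptions the two-month effect of 0.30 SD is estimated at about 0.34 to 0.41 SD with an independence or school-level exchangeable correlation, and at about 0.30 SD with a pupil-level exchangeable correlation and a normal outcome. The three-time-point average moves by about 0.015 to 0.035 SD.

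It would be wrong to read this as a forecast that the trial will overstate its effect by 15 to 35%. That range needs loss that depends on scores in one arm and not the other, and the documents supply neither that mechanism nor the correlation. Loss that merely differs in amount between arms does no harm. This is a worthwhile correction to the analysis, not a flaw that invalidates the trial.

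**What to change.** In the Statistical analysis section, follow the missing-data sentence with, or replace it by, a main analysis that is valid under missing at random and uses the baseline and post-intervention scores of pupils later lost. Either of these would serve:

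- multiple imputation within arm from baseline and earlier scores, with school in the imputation model, followed by the GEE; or
- a likelihood-based mixed model on all observed assessments, with pupil and school effects and small-sample degrees of freedom.

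Keep the available-case GEE as a sensitivity analysis and state its working correlation and clustering level. Add a not-at-random sensitivity analysis, because methods valid under missing at random remain biased if loss follows the unseen two-month response. Show loss by arm and school in the CONSORT flow diagram already promised.

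The cost is revised wording and a little more programming; no new data are needed. The drawback is reliance on a parametric model with only four schools, which leaves about 4 − 2 = 2 degrees of freedom between schools for the arm comparison, so the small-sample method must be named in advance.
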